##### Sensitivity analysis

The main analysis, without subgroup analyses, will be repeated on the PP set. Potential deviations from the results of the ITT analysis will be described in detail.

##### Secondary analysis

The secondary (exploratory) objectives are to assess the therapeutic efficacy of externally induced mild ketosis by the IMP regarding the following secondary endpoints:change in number of headache days of any severity from baseline (meeting ICHD-3 criteria) during the last 4 weeks of intervention;change in number of headache days of any severity from baseline (meeting ICHD-3 criteria) during the last 4 weeks of follow-up;change in consumption of acute migraine medication from baseline (analgesics or triptans)— measured in days with acute headache medication use—during the last 4 weeks of intervention;change in average migraine intensity from baseline—assessed with a VAS from 0 to 10 for each migraine episode—during the last of 4 weeks of the intervention period; andchange in disability from baseline—assessed with the Migraine Disability Assessment (MIDAS) and the Headache Impact Test (HIT-6)—to the last of 4 weeks of the intervention period.

All of these secondary endpoints will be analysed as described for the primary endpoint with the corresponding baseline measure as covariate, if available.

All secondary analyses are done on the ITT set.

##### Exploratory analyses

The exploratory objectives are to assess the potential mechanisms of action of externally induced mild ketosis by the IMP regarding markers of oxidative stress, markers of inflammation, glucose, fat, protein metabolism and genetic analyses:Serum concentration changes from baseline of oxidative and nitrosative stress markers (malondialdehyde (MDA), carbonylated proteins, nitrate, nitrite, nitrotyrosine) using ELISA and mass spectroscopy. This exploratory endpoint will be analysed as described for the primary endpoint with the corresponding baseline measure as a covariate.Serum concentration changes from baseline in markers of fat (triglycerides, cholesterol, HDL, LDL) or glucose metabolism (insulin, glucose, cortisol, Hba1c and lactate) during the last 4 weeks of intervention. This exploratory endpoint will be analysed as described for the primary endpoint with the corresponding baseline measure as a covariate.Serum concentration changes from baseline in serum inflammatory markers (cytokines including, but not limited to, IFN-γ, IL-1β, IL-2, IL-4, IL-5, IL-6, IL-10, MCP-1, TNF-α, TNF-β, TGF-β1) during the last 4 weeks of intervention, using a multiplex immunoassay analysed with a BioPlex 200. This exploratory endpoint will be analysed as described for the primary endpoint with the corresponding baseline measure as a covariate.

The following exploratory endpoints will be analysed with standard methods for gene and/or gene expression variation analysis:genetic profile (single nucleotide polymorphisms (SNPs)) of all patients involved in the study and correlation of the genetic markers with other outcome measures;gene expression changes before and after diet using expression microarrays with a special focus on mitochondrial-related genes (citrate synthase, cytochrome C oxidase subunit 1, succinate dehydrogenase subunit A); andcorrelation of gene expression changes with the genetic profile of the patients (eQTL analysis in combination.

All exploratory analysis is done on the ITT set.

##### Safety analysis

Safety and tolerability will be determined by:comparison of treatment-emergent adverse events (any event regardless of potential causality with the drug) and treatment-related adverse events as defined by the principal investigator between active treatment and placebo; andexamination for potential effects of the intervention on routine laboratory parameters (renal and liver function tests, electrolytes, full blood count, CRP, lipids, Hba1c, insulin, cortisol, lactate, TSH, FT4, FT3) in the treatment group compared to the control group.

##### Deviation(s) from the original statistical plan

If substantial deviations of the analysis as outlined in these sections are needed for whatever reason, the protocol will be amended. All deviations of the analysis from the protocol or from the detailed analysis plan will be listed and justified in a separate section of the final statistical report.

#### Handling of missing data and drop-outs

The frequency of, timing of and reasons for, as well as all side-effects of, drop-outs will be reported for each treatment. Patients who drop out during the first run-in period or during the first 4 weeks of the first treatment period will be excluded. All patients who drop out later will be included in the ITT set.

For patients who drop out after the first 4 weeks and before the end of the first treatment period, the primary endpoint for the first treatment period will be imputed using multiple imputations. If appropriate, imputations will be accounted for baseline value and number of migraine days during the first treatment period, as far as available. The primary endpoint for the second treatment period will not be imputed for these patients.

For patients who drop out after the end of the first treatment period and before the first 4 weeks of the second treatment period are finished, the primary endpoint for the second treatment period will not be imputed. The primary endpoint for the first treatment period will be available.

For patients who drop out after the first 4 weeks and before the end of the second treatment period, the primary endpoint for the second treatment period will be imputed as already described.

Thus, for each patient included in the ITT set, the primary endpoint will be available (whether measured or imputed) for at least the first treatment period and will be taken into account with the proposed mixed effects models.

In case there are indications for missing data not at random, the inverse probability of censoring weights (IPCW) will be considered.

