#### Fixed sample size estimation

##### Assumptions

Sample size estimation is based on the following assumptions:We expect the baseline number of migraine days per 4 weeks to be 10 days in our patient population.Placebo effect: based on recent findings [64], we assume a rather strong placebo effect of 32% reduction in the primary endpoint. This corresponds to an absolute reduction of 3 migraine days per 4 weeks.IMP effect: synthesising previous findings [4, 64] and our pilot data [65], we aim to detect a difference of 2 days between placebo and IMP.We assumed the absolute reduction in migraine days to be normally distributed with a standard deviation of 3 days.We assume a conservative intra-patient correlation between IMP and placebo of 0.4.Drop out: a high drop-out rate of 30% is assumed.

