##### Re-sampling

The sample size was estimated using a re-sampling method. Each sample size (n_i_ = 1,...,49 = 12, ..., 60) was evaluated by sampling *R* = 999 times the reduction in migraine days from a bivariate normal distribution as already described. For each sample, whether superiority of the IMP over placebo could be shown (i.e. whether a two-sided paired *t* test resulted in significant *p* < 0.05) was tested.

In order to show the superiority of the IMP over placebo with a statistical power of 90%, 45 patients should be recruited in total to ensure 31 evaluable patients, assuming a drop-out rate of 30%. Figure 3 shows how the sample size depends on the expected reduction in number of migraine days in the IMP arm.

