#### Hypothesis

The *null hypothesis* is that there is no difference in the difference in number of migraine days per 4 weeks from baseline to the last 4 weeks of intervention between the IMP and the placebo treatment.

The corresponding *alternative hypothesis* is that the difference in the number of migraine days per 4 weeks from baseline to the last 4 weeks of intervention differs between the IMP and the placebo treatment.

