##### Primary analysis

The primary endpoint, the number of migraine days in the last 4 weeks of treatment, will be measured twice for each patient, once after the placebo treatment period and once after the IMP treatment period. The number of migraine days in the 4 weeks before start of treatment will be assessed for both treatment periods, thus there will be two baseline values that will be used as covariates. This process has the aim of correcting for any potential seasonal variation in baseline migraine frequency or carry-over effects.

The primary analysis will be performed using a linear, mixed-effects regression model. The primary model will include the primary endpoint (the number of migraine days in the last 4 weeks of treatment) as the response variable, the respective baseline value as a covariate, treatment (IMP vs placebo) and period (first vs second) as main effects, the two interaction terms “treatment × period” and “treatment × baseline value”, and patient as random effects. A significant interaction term between treatment and period would indicate a carry-over effect. Since it is not known how strongly the primary endpoint correlates with the baseline value, it is not known whether including the baselines as covariates in the model is sensible. Therefore, the already described primary model will be compared to models without the interaction term “treatment × baseline value” and without both the interaction term “treatment × baseline value” and the baseline value as a covariate by means of Akaike’s Information Criterion (AIC).

The primary analysis will be done on the ITT set.

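### The predictors named for multiple imputation do not include treatment, and the rule for second-period drop-outs is ambiguous; followed as written, imputation shrinks the IMP-placebo difference

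*Protocol article*

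**What the plan says.** The section Handling of missing data and drop-outs of the protocol article imputes the primary endpoint by multiple imputation for patients who complete the first 4 weeks of a treatment period but not the whole period. In the paragraph on first-period drop-outs, and after a conditional hedge, it names the inputs: "imputations will be accounted for baseline value and number of migraine days during the first treatment period, as far as available". For patients who drop out after week 4 of the second period, "the primary endpoint for the second treatment period will be imputed as already described". Drop-outs within the first 4 weeks of either period, or between periods, get no imputed value for the period they did not complete. Neither treatment nor sequence is named as an input.

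The imputed values enter the primary analysis, which is run on the ITT set. Its model has "treatment (IMP vs placebo) and period (first vs second) as main effects", plus the period's baseline, treatment by period, treatment by baseline and a random patient effect. The Hypothesis section compares IMP with placebo and words its null as follows: "there is no difference in the difference in number of migraine days per 4 weeks from baseline to the last 4 weeks of intervention". On drop-out, the sample-size section says that "a high drop-out rate of 30% is assumed", without dividing it by period or week.

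**The concern.** An imputation model should contain at least the terms that the analysis model estimates. If treatment is left out, missing endpoints on IMP and on placebo are drawn from one common prediction, and any difference between them must come through the other predictors. Early on-treatment migraine days carry part of the treatment effect, so the imputed contrast is weakened but need not vanish.

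The crossover adds a second problem. If the back-reference for the second period is taken at its word, the predictor is the first-period count, recorded on the other treatment. A patient who had IMP first, and so tends to have fewer migraine days, would then get a low imputed value for the placebo period, and the reverse for placebo first.

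At stake are the size of the primary estimate and power in a 45-patient trial. This happens even when drop-out is unrelated to outcome, so the inverse-probability weighting that the section holds in reserve does not address it.

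**Working it through.** **Inputs from the protocol article.** Baseline 10 migraine days per 4 weeks; "we aim to detect a difference of 2 days between placebo and IMP"; SD of the reduction 3; within-patient correlation 0.4; drop-out 30%; 1:1 AB/BA allocation.

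**The plan's own figure.** SD of the paired difference = 3 × √(2 × (1 − 0.4)) = 3.286. With a difference of 2 and a two-sided 0.05 paired *t* test, power is 89.6% at n = 30 and 90.6% at n = 31. Then 31 / 0.70 = 44.3, rounded up to 45. The stated 31 evaluable and 45 recruited reproduce, so the sample size is not in question.

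**Hand check of the literal reading.** Take reductions in migraine days and pool the sequences without treatment. The within-sequence covariance of the two periods is 0.4 × 9 = 3.6. The sequence means lie ±1 day apart from the centre in opposite directions, which adds −1 to the covariance and +1 to the variance. The slope of period 2 on period 1 is (3.6 − 1) / (9 + 1) = 0.26. The sequences differ by 2 days in period 1, so imputed period-2 migraine days show an IMP-placebo contrast of about 0.26 × 2 = +0.5 days, where the truth is −2.

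**Simulation.** AB/BA trials used the inputs above, multiple imputation, and a random-intercept model with baseline, treatment and period (without the two interactions). Assumed, because the article does not give them:
- baseline SD 2.5;
- correlation between 4-week blocks 0.5, 0.7 or 0.85;
- effect full from the first block, or 50/75/100% over the three blocks;
- drop-out unrelated to outcome;
- the imputed shares in the table.

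Shrinkage of the 2-day effect in large samples, relative to the same recipe with treatment added:

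| Imputed, period 1 + period 2 | Own-period days, no treatment | First-period days for period 2, no treatment |
|---|---|---|
| 5% + 5% | 1-3% | 3-4% |
| 10% + 10% | 1-7% | 7-9% |
| 15% + 15% | 2-10% | 11-14% |
| 0% + 30% | 2-11% | 17-18% |

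With treatment in the imputation model, the estimate lay between −1.97 and −2.03 in every case.

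Among imputed values only, against a true −2.0, the IMP-placebo contrast was:
- about −0.5 to −1.8 in period 2 from own-period days;
- about −0.4 to −1.7 in period 1;
- about +0.2 to +0.5 in period 2 from first-period days.

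**Cross-check of the last row.** Period 1 is intact at −2. Average the two periods equally:
- first-period days, imputed contrast +0.4: period 2 = 0.7 × (−2) + 0.3 × 0.4 = −1.28; mean −1.64; shrinkage 18%;
- own-period days, imputed contrast −0.6: period 2 = −1.58; mean −1.79; shrinkage 10.5%;
- own-period days, imputed contrast −1.8: period 2 = −1.94; mean −1.97; shrinkage 1.5%.

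These agree with the simulated 17-18% and 2-11%.

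**Power at N = 45** (300 simulated trials, Monte Carlo error about 2 points), without versus with treatment in the imputation model:

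| Imputed | Own-period days | First-period days for period 2 |
|---|---|---|
| 5% + 5% | 96% vs 97% | 95% vs 95% |
| 15% + 15% | 90% vs 95% | 83% vs 92% |
| 0% + 30% | 88% vs 92% | 79% vs 88% |

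**A second simulation** spread the 30% drop-out over calendar time instead of fixing imputed shares. It gave shrinkage of 1-9% with own-period days. With first-period days it gave about 8% if drop-out is even over 32 weeks, and 14-16% if all of it falls in weeks 5-12 of the two periods.

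**The case against.** A reader might infer that the protocol prescribes first-period days for second-period drop-outs, so that imputed patients show no treatment difference or one of the wrong sign. The text does not establish this. The predictor sentence stands in the paragraph on first-period drop-outs, where first-period days are simply the days recorded in the interrupted period. The section also imputes a second-period endpoint only after 4 weeks of that period, although first-period data would be complete without this condition. The threshold makes most sense if own-period days are meant. On that reading imputed patients keep part of the treatment contrast, and the shrinkage is the smaller of the two ranges.

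A reader might also infer that the plan excludes treatment. It does not: the list opens with a hedge, is not called exhaustive, and detailed methods are left to the statistical analysis plan, which is not shown and may add treatment.

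The size can be small. Only drop-outs after week 4 of a period are imputed, so 30% imputed is an upper bound; at 5% + 5% the power loss is within simulation error. In the second simulation, power on the literal reading stayed above the planned 90% (95.4% vs 98.4% with drop-out confined to the treatment weeks; 91.8% vs 98.6% with all of it in weeks 5-12).

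All of this limits the size. It does not remove the point. The article goes beyond silence by naming predictors; the hedge adds none to the list; and a back-reference that supports two readings should not govern the primary analysis. Shrinkage appeared on both readings.

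**Conclusion.** The point holds in a limited form. The named predictors omit treatment, and an imputation model confined to them biases the primary estimate toward no difference. For first-period drop-outs this does not depend on how the back-reference is read. For second-period drop-outs the back-reference is ambiguous. Over the assumed scenarios the overall shrinkage is roughly 1-11% with own-period days, the more natural reading, and roughly 3-18% with first-period days.

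The bias is conservative. If the treatments do not differ, treatment carries no information for the imputation and leaving it out creates no false difference, so type I error is not inflated. This was reasoned, not simulated. The cost is an understated effect and, when many endpoints are imputed, some loss of power.

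The sizes rest on the imputed share, the speed of onset, the correlation between 4-week blocks and drop-out unrelated to outcome, none of which the article gives. It is worth correcting before analysis, but it does not invalidate the design or the sample size.

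**What to change.** In Handling of missing data and drop-outs, state that each period's missing endpoint is imputed from the treatment received in that period, that period's baseline, and the migraine days already recorded in that same period. Other-period data may be added, but only alongside treatment. Any treatment interaction kept in the analysis model should also be in the imputation model. Replace the back-reference for the second period with this explicit rule, and carry the same wording into the statistical analysis plan.

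This takes one or two sentences and needs no new data or patients. The small downside is one or two more parameters in an imputation model fitted to few patients. Because the article requires a protocol amendment for substantial departures from the outlined analysis, it is cleaner to settle this before database closure. Leaving out imputation and fitting the mixed model to observed endpoints was also unbiased in the second simulation, but that is a choice between valid methods and not a required correction.

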#### Planned analyses

##### Datasets to be analysed, analysis populations

The full analysis set (FAS) consists of all patients who are randomised and for whom the number of migraine days per 4 weeks at baseline is available.

The intention to treat (ITT) will include all randomised patients for whom the number of migraine days of at least the first 4 weeks of the first treatment period is available.

The per protocol (PP) will include all patients from the ITT set for whom the primary endpoint is available for both treatment periods, who are compliant as per the protocol (see later) and who have no protocol violations (to be defined in detail in the statistical analysis plan).

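### IPCW is named as the remedy for data missing not at random but is valid only under missing at random, so no analysis stated in the protocol examines informative drop-out

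*Protocol article*

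**What the plan says.** The section *Handling of missing data and drop-outs* sets rules by the time of leaving:

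- Before treatment or early in period 1: "Patients who drop out during the first run-in period or during the first 4 weeks of the first treatment period will be excluded".
- Later in period 1: "the primary endpoint for the first treatment period will be imputed using multiple imputations". Where appropriate, "imputations will be accounted for baseline value and number of migraine days during the first treatment period, as far as available". For the other period: "The primary endpoint for the second treatment period will not be imputed for these patients".
- After period 1 but before week 4 of period 2 is complete: the first endpoint is used and the second is not imputed.
- Later in period 2: the second endpoint is imputed in the same way.

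Imputed and measured endpoints then enter the linear mixed model of *Primary analysis*. For departures from MAR the section offers one tool: "In case there are indications for missing data not at random, the inverse probability of censoring weights (IPCW) will be considered". It also asks for a descriptive report, by treatment, of how often, when and why patients leave.

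The section *Sensitivity analysis* lists one item: "The main analysis, without subgroup analyses, will be repeated on the PP set". Under *Datasets to be analysed, analysis populations*, that set is limited to ITT patients "for whom the primary endpoint is available for both treatment periods" who also meet the compliance and violation criteria. Under *Assumptions* for the sample size, "a high drop-out rate of 30% is assumed".

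**The concern.** IPCW gives more weight to patients who stayed and who resemble, on recorded variables, those who left. If leaving also depends on the migraine days that were never recorded, no weight built from recorded variables can correct for it. The sentence therefore assigns an MNAR role to a method that needs MAR.

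The sentence is also conditional twice over: it needs indications of MNAR, and even then IPCW is only to be considered. Outcome data alone cannot separate MAR from MNAR, so a check on the diary data would not settle whether the condition is met.

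What is at stake is how the primary result can be read. Suppose patients who leave on one treatment do worse than their recorded data predict. The imputed analysis and the IPCW analysis would then carry much the same bias, and agreement between those two would say nothing about MNAR. An analysis plan that followed the sentence would inherit the error.

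**Working it through.** **1. What each stated element assumes.**

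| Element | Data used | Does it test MNAR? |
|---|---|---|
| Multiple imputation, weeks 5-12 of a period | Baseline and the patient's own recorded migraine days | No, MAR |
| Endpoints not imputed, left to the mixed model | Observed endpoints | No, MAR |
| Leavers in the first 4 weeks of period 1 | None, excluded | No |
| Per-protocol repeat | Patients with both endpoints | No |
| IPCW | Variables in the weight model | No, MAR given those variables |

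For the per-protocol set, the missing-data section counts imputed endpoints as available. If the word means measured, every patient lacking an endpoint is dropped. If it includes imputed values, the MAR imputation is reused. Neither is an MNAR test.

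**2. The plan's own figure.** Inputs from *Assumptions* and *Re-sampling*: SD 3, correlation 0.4, difference 2 days, two-sided 0.05, paired t test.
- SD of the difference = √(2 × 3² × (1 − 0.4)) = √10.8 = 3.286.
- Exact power is 0.896 at n = 30 and 0.906 at n = 31, so 31 evaluable patients.
- 31/0.7 = 44.3, rounded up to 45. The stated 31 and 45 reproduce.
- Smallest significant difference at n = 31: 2.042 × 3.286/√31 = 2.042 × 0.590 = 1.205 days.

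**3. Does IPCW help under MNAR?** A simulation with 1,000,000 patients per arm had 30% drop-out on IMP only. The endpoint had SD 3 and correlation 0.5 with an observed early change. Weights and imputation both used that early change. The arms were simulated as independent groups to isolate the missing-data mechanism, and all settings beyond the SD, the 30% and the 2-day effect are assumptions.

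| Leaving depends on | Truth | IPCW | MAR imputation | Complete cases |
|---|---|---|---|---|
| Observed early change | 2 | 2.00 | 2.00 | 2.49 |
| Unseen endpoint, log-odds 0.25 per day | 2 | 2.46 | 2.46 | 2.60 |
| Unseen endpoint, log-odds 0.5 per day | 2 | 2.78 | 2.78 | 2.98 |
| Unseen endpoint, log-odds 1 per day | 2 | 3.07 | 3.06 | 3.28 |

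With a true effect of 0, the three MNAR settings gave 0.46, 0.79 and 1.07 for IPCW and 0.46, 0.78 and 1.06 for imputation. IPCW works under MAR. Under MNAR it reproduces the bias of the imputation. The sizes are a one-arm worst case and do not forecast this trial.

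**4. Illustrative size.** Let f be the share of a treatment's endpoints that are imputed and D the days by which those patients are worse than imputed. Then

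net bias in favour of IMP ≈ f(IMP) × D(IMP) − f(placebo) × D(placebo).

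The protocol gives none of the four. With the placebo term at zero:
- f = 0.10, D = 1: 0.10 day, which is 8% of 1.205.
- f = 0.15, D = 3: 0.45 day, which is 37% of 1.205.

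For scale on f: 30% of 45 is 13.5 leavers. Spread evenly over 32 weeks and equally by treatment (assumption), about 13.5 × 16/32 × 1/2 = 3.4 of roughly 39 IMP endpoints would be imputed, or 9%. The 10-15% range therefore needs drop-out to concentrate on IMP or in weeks 5-12.

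**5. How far MAR must fail.** An observed difference of exactly 2 days loses significance at D = (2 − 1.205)/f: 8.0 days for f = 0.10, 5.3 for f = 0.15 and 2.7 for f = 0.30. A result nearer 1.2 days would be more fragile. Using the n = 31 threshold with a non-zero imputed share is an approximation, because 31 counts patients left after drop-out while imputed endpoints belong to the larger ITT set.

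**The case against.** The strongest reply is that this is a condensed article, that *Statistical analyses* defers detailed methodology to a statistical analysis plan not shown, and that MNAR sensitivity analyses commonly sit there. That stands as far as it goes. A reader might infer that nothing will test the primary result against informative drop-out, and the documents do not support that. The point rests on what the protocol states: it names a method for MNAR, and the method is the wrong one.

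Four other inferences also go too far.
- *Every planned analysis rests on one assumption.* The per-protocol repeat, if limited to measured endpoints, rests on a different and stronger condition, and step 3 shows complete cases giving different values. It is still no MNAR test.
- *Leavers are imputed as if they were completers.* The imputation may use each leaver's own recorded migraine days, so someone leaving with many of them would be imputed high. Only the part that those days do not explain is at issue.
- *The trigger can never work.* Reasons for leaving and side-effects are recorded by treatment and can legitimately raise suspicion. IPCW using them could correct drop-out that the imputation model misses. That is MAR on a wider set of variables, which is useful but not a remedy for MNAR.
- *The treatment effect is overstated.* With equal departures on both treatments the net bias is zero. If leaving for lack of effect is commoner on placebo, it runs against IMP. The placebo can also cause gastrointestinal symptoms, so the direction cannot be presumed.

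**Conclusion.** The point holds as a specific error in the text. IPCW is valid only under MAR given the variables in its weight model, so it cannot serve as the response to MNAR. The imputation and the mixed model also rely on MAR, the per-protocol repeat does not test MNAR, and early leavers are excluded. No analysis stated in this protocol therefore examines informative drop-out, with 30% drop-out planned for.

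Size and direction are unknown. The range of 0.1-0.45 day, against about 1.2 days, rests on three assumptions that the protocol does not supply: 10-15% of IMP endpoints imputed, those patients 1-3 days worse than imputed, and no matching shift on placebo. At the planned 2-day effect, shifts of that size alone would not remove significance; nearer the threshold they could. The trial is not invalidated and the sample size of 31/45 is unaffected. The sentence should be corrected before the analysis plan is finalised.

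**What to change.** Relabel IPCW as an alternative MAR analysis. It is worth keeping if its weight model adds predictors that the imputation lacks, such as adverse events or reason for leaving.

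Replace its MNAR role with a pre-specified delta-adjusted (tipping-point) multiple imputation of the primary endpoint, run whatever the data suggest:
- Vary delta separately for IMP and placebo, so that bias in either direction is visible.
- Include the endpoints now left unimputed and the randomised patients excluded for leaving in the first 4 weeks of period 1. The full analysis set already defined, randomised with a baseline count, is a natural basis. Where the second baseline is also missing, it must be imputed too.
- Report the delta at which the conclusion changes, and extend the grid until it does. Step 5 shows that stopping at 3 days would not reach that point at a 2-day effect with 10-15% imputed.

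The cost is wording in the analysis plan and repeated runs of imputation code that is already needed. No new data, visits or patients are required.
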